### Sample size determination

According to the latest report from the Department of Health on coverage of the HPV vaccinations [7], the average completion rate for the “catch-up” campaign targeting females aged 17-18 years in the Birmingham East & North Primary Care Trust is 32.4%. Previous studies investigating the impact of financial incentives on uptake of vaccinations have reported an avergage between-group difference of approximately 8.5%: Specifically, Moran et al. [17] reported an effect size of 8.5% for uptake of the influenza vaccination with incentives (20.3% (control group) vs 28.8% (incentivised group)) and Yokley et al. [18] reported an avergage increase of 8.4% in childhood immunisation across three time points with the addition of inventives (at two weeks: 10.1% (control group) vs. 22.5% (incentivised group); at 2 months: 22.7% (control group) vs. 30.8% (incentivised group); at three months: 26% (control group) vs 30.8% (incentivised group)). Based on these figures, we expect financial incentives in this study to increase completion (i.e. uptake of the 3^rd^ vaccination) of the HPV vaccination programme by 8.5%, resulting in a completion rate of 40.9% by incentivised groups. To detect this difference between arms using a two-tailed *χ*^2^ test at the 5% significane level with 80% power, a sample of 1008 participants is required (calculations performed in GPower 3.0); This figure has been rounded off to the nearest whole number, resulting in a required sample of 1000 participants (half of whom consist of previous-non attenders and half of whom, first-time invitees), giving 500 in each intervention arm (See Table 1).

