### Statistical analysis

To assess the impact of the intervention on initial uptake (i.e. the 1st vaccination) and completion of the HPV vaccination programme (i.e. the 3rd vaccination) logistic regressions will be performed separately for each of the two samples, i.e. for girls who have not received an invitation to get vaccinated before and those who have received a previous invitation but have failed to attend. To test the moderating effect of social deprivation on the impact of the intervention, the interaction between IMD scores and intervention will be added to the logistic regression models. To test whether there is a difference in the size of effect of the intervention in the two samples, datasets will be combined and another logistic regression conducted, in which whether participants have received an invitation to get vaccinated before or or not will be added as a predictor to the model, along with the intervention. To test for differences in the attrition rates between the 1^st^ and 3^rd^ vaccinations between the invervention and control groups the *χ*^2^ test will be used. Finally, differences in knowledge of the HPV vaccination between intervention and control group will be tested using the *χ*^2^ test, while differences in attitudes towards the HPV vaccination will be examined via a one-way analysis of variance. All tests will be assessed at the 5% level of significance.

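### The combined model meant to compare the incentive effect between the two samples has no interaction term, so it cannot make that comparison

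*Protocol article*

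**What the plan says.** The Statistical analysis section of the protocol article plans separate logistic regressions of first and third vaccination in each of the two samples. It then turns to the comparison between samples and states the purpose: "To test whether there is a difference in the size of effect of the intervention in the two samples, datasets will be combined". For this, whether a girl had been invited before "will be added as a predictor to the model, along with the intervention". No product of prior invitation and intervention is named there or elsewhere in the article.

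The sentence just before handles the other moderation question differently. For deprivation, "the interaction between IMD scores and intervention will be added to the logistic regression models". The section closes with a common threshold: "All tests will be assessed at the 5% level of significance".

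**The concern.** A difference in the size of an effect between two groups is effect modification. In a regression it is carried by an interaction term. The model described has only the main effects of intervention and prior invitation, so it assumes the quantity in question to be zero.

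Someone who follows the text has two coefficients to look at. One is the incentive effect averaged over both samples. The other is the adjusted difference in uptake between previous non-attenders and first-time invitees. Reading the second as the test of effect difference would confuse who gets vaccinated more often with who responds more to the incentive. The two samples could plausibly differ in uptake whatever the incentive does, because one of them is defined by having missed an earlier first appointment.

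What is at stake is the only formal comparison of the incentive effect between the two samples.

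**Working it through.** **1. Inputs from the protocol article**
- Control completion: "in the Birmingham East & North Primary Care Trust is 32.4"% (Sample size determination).
- Incentive completion: "resulting in a completion rate of 40.9% by incentivised groups" (same section).
- Design test: two-tailed, "at the 5% significane level with 80% power" (same section).
- Cells: 250 girls in each of the four combinations of arm and sample (Table 1).

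**2. The protocol's own figure.** The mean rate is (0.324 + 0.409)/2 = 0.3665 and the difference is 0.085.

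n per arm = [1.960·√(2·0.3665·0.6335) + 0.842·√(0.324·0.676 + 0.409·0.591)]² / 0.085² ≈ 503.3, rounded up to 504.

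The total is 1008, as stated. The inputs are therefore understood correctly. The point below does not depend on this figure.

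**3. What each model estimates.** Let A = 1 for incentive and S = 1 for previous non-attender.
- As written: logit(p) = β0 + β1·A + β2·S. The log odds ratio for the incentive is β1 when S = 0 and β1 when S = 1. The difference is zero by construction, and β2 is a difference in uptake level.
- With the interaction: logit(p) = β0 + β1·A + β2·S + β3·A·S. The log odds ratios are β1 and β1 + β3. The difference is β3, which is the quantity the stated purpose needs.

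**4. Same effect, different uptake levels.** The design odds ratio is (0.409/0.591)/(0.324/0.676) = 1.444. It was applied to both samples, with first-time control completion at 32.4%. The protocol gives no rate for previous non-attenders, so a range is assumed. Each scenario had 10,000 simulated trials with 250 per cell and two-sided Wald tests at 5%.

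| Assumed non-attender control rate | Prior-invitation term significant (model as written) | Interaction significant |
|---|---|---|
| 32.4% | about 5% | about 5% |
| 27% | about 48–49% | about 5% |
| 22% | about 97% | about 5% |
| 15% | about 100% | about 5% |

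The effects are identical on the odds-ratio scale, which is the scale of the planned model.

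**5. Different effects, equal mean uptake**
- Incentive effect +17 points in one sample (28.15% to 45.15%) and 0 in the other (36.65% in both arms): prior-invitation term significant in about 5%, interaction in about 80%.
- Incentive effect +8.5 points in one sample and −8.5 in the other (32.4% to 40.9%, and the reverse): about 5% and about 80%.

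**6. Power of the correct test at the design effect.** Take +8.5 points in one sample and 0 in the other, with 32.4% in the three cells without an effect.
- log odds ratio = ln 1.444 = 0.367
- V = 3/(0.324·0.676) + 1/(0.409·0.591) = 3·4.566 + 4.137 = 17.83
- Standard error with 250 per cell = √(17.83/250) = 0.267
- Power ≈ Φ(0.367/0.267 − 1.960) = Φ(−0.585) ≈ 0.28. Simulation gives 27–28%.
- For 80% power: (1.960 + 0.842)²·17.83/0.367² ≈ 1,040 per cell, about 4,150 girls in total.

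**The case against.** **It is a supporting analysis.** The comparison between samples is not among the objectives, the three hypotheses or the key results named in the abstract. Uptake is analysed separately in each sample, which matches the separate randomisation, and those regressions give a valid incentive effect in each sample whatever the combined model contains. This stands. A reader might infer that the trial's conclusion on who benefits from incentives would be wrong. The documents do not support that, because the per-sample odds ratios would still be available. Only the formal test of their difference is affected.

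**The text does not name the coefficient to be tested.** It gives a purpose and a list of predictors, so the analysts might have an interaction in mind, or a fuller analysis plan might state it. This stands in part: misuse of the prior-invitation term is a risk, not a certainty. It does not remove the fault. The article names a particular model for a particular question, and that model cannot answer it. The deprivation sentence shows that the authors write out an interaction where they intend one.

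**The error rate depends on unknown uptake.** A reader might infer that a false difference is almost certain to be reported. That holds only where control uptake differs widely between the samples. At 27% against 32.4% it is about an even chance, and at equal rates there is no inflation. The protocol gives only a trust-wide figure, so the whole range has to be shown.

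**The fix is less powerful than it looks.** Power near 80% arises only when the effects differ by 17 points, twice the design effect of 8.5 points. This stands, and the low power at the design effect has to be stated with the fix.

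**Conclusion.** The point holds, limited to the between-sample comparison. As written, the combined model forces a common odds ratio on both samples and has no term for a difference in effect. If its prior-invitation coefficient were read as that test, it would be significant in anything from about 5% to 100% of trials with identical effects. The rate depends on a gap in control uptake that the protocol does not give. The coefficient would also detect a real difference no better than chance when mean uptake is equal.

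That the model does not match its aim follows from algebra and needs no assumption. The rejection rates rest on the assumed non-attender control rates, a constant odds ratio of 1.44, and 250 girls per cell with complete uptake data. The per-sample results for first and third vaccination are not put in doubt. The correction should be made, but it ranks below a fault that would undermine the trial's main conclusions.

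**What to change.** In the Statistical analysis section, state that the combined logistic model contains intervention, prior invitation and their interaction. State also that the test of a difference in effect is the Wald or likelihood-ratio test of the interaction, and that the interaction is reported as a ratio of odds ratios with its 95% confidence interval. Present it beside the two per-sample odds ratios.

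Add one sentence on precision: with 1000 girls, power is about 28% if the incentive adds 8.5 points in one sample and nothing in the other, so a non-significant interaction will not be read as equal effects.

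The cost is two sentences of text. No extra data or participants are needed, and the sample size and the per-sample analyses stay as they are.

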### Hypothesis I

Those offered financial incentives to get vaccinated against HPV are more likely to receive the first and third HPV vaccinations.

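### The chi-square test of attrition between doses 1 and 3, read naturally, compares only girls who took dose 1, so it is not a randomised comparison and can show worse dropout when completion is equal or better

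*Protocol article*

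**What the plan says.** The Statistical analysis section gives first- and third-dose uptake to models in which "logistic regressions will be performed separately for each of the two samples". To compare the effect between samples, "datasets will be combined and another logistic regression conducted". The next sentence begins "To test for differences in the attrition rates between the" first and third vaccinations and assigns a chi-square test of the intervention group against the control group. It names neither a denominator nor a stratification. The section ends "All tests will be assessed at the 5% level of significance", so the attrition comparison is a significance test and not a descriptive table.

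Two other places bear on it. The Procedure section makes each dose conditional on the earlier ones, so only a girl who took dose 1 can drop out before dose 3. Hypothesis I reads: "Those offered financial incentives to get vaccinated against HPV are more likely to receive the first and third HPV vaccinations".

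**The concern.** Randomisation makes the two arms comparable as invited. It does not make the girls who take dose 1 comparable if the incentive changes who they are, and the first hypothesis says it will bring in more of them. The incentive arm's starters would then include girls who would not have started without vouchers, and the control arm's would not. If those added girls complete less often than the others, attrition among starters rises in the incentive arm even though nobody who would have started anyway behaves differently.

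The Discussion section recognises this kind of selection, saying that incentives may change who attends and that the design cannot separate this from other effects. It says so only for informed choice, and the attrition test carries no such caution. A significant result could be read as showing that paying girls makes them more likely to abandon the course, beside a completion result that is equal or favours incentives.

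**Working it through.** **Calibration.** The attrition test has no planned figure of its own, so the method was first checked on the sample size. Inputs from Sample size determination: control completion "in the Birmingham East & North Primary Care Trust is 32.4"%, incentive arm "resulting in a completion rate of 40.9% by incentivised groups", two-sided 5%, 80% power. With p̄ = (0.324 + 0.409)/2 = 0.3665:

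n per arm = [1.96·√(2·0.3665·0.6335) + 0.8416·√(0.324·0.676 + 0.409·0.591)]² / 0.085² ≈ 503.3, rounded up to 504, total 1008. This matches "level with 80% power, a sample of 1008 participants is required".

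**Inputs for attrition.** The Background gives 62.2% (dose 1) and 31.8% (dose 3) for the England catch-up campaign. No dose-1 rate is given for the local Trust, so the England pair is used for both samples together. Arm size is 500. The size of the rise in dose-1 uptake and the share of added starters who complete are not in the document; both are assumed and varied.

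**Formulas.** Attrition among starters = 1 − dose 3/dose 1.
- Control: 1 − 31.8/62.2 = 48.9%, on 0.622 × 500 = 311 starters.
- Incentive, with d added points of starters and share s of them completing: 1 − (31.8 + s·d)/(62.2 + d).
- Chance of a significant result in the worse direction: Φ[(difference − 1.96·SE₀)/SE₁], with SE₀ pooled and SE₁ unpooled, on the expected numbers of starters. With no true difference this is 2.5%.

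**One cell in full** (d = 8.5, s = 25%). Dose 3 = 31.8 + 2.125 = 33.925%. Dose 1 = 70.7%, or 353.5 starters. Attrition = 1 − 33.925/70.7 = 52.0%. The difference is 0.0314, SE₀ = 0.0389 and SE₁ = 0.0389, so Φ(−1.15) = 12.5%.

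| Added starters (points) | s = 0: attrition, chance | s = 25%: attrition, chance | s = 40%: attrition, chance |
|---|---|---|---|
| 8.5 | 55.0%, 35.3% | 52.0%, 12.5% | 50.2%, 5.3% |
| 12 | 57.1%, 57.8% | 53.1%, 19.5% | 50.7%, 6.8% |
| 15 | 58.8%, 74.5% | 54.0%, 26.5% | 51.0%, 8.2% |
| 20 | 61.3%, 91.6% | 55.2%, 39.5% | 51.6%, 10.7% |

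Completion among all randomised girls in the incentive arm is 31.8% when s = 0 (equal to control), 33.9% to 36.8% when s = 25%, and 35.2% to 39.8% when s = 40%.

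**When the sign turns.** Attrition looks worse whenever added starters complete at less than the control starters' rate, 31.8/62.2 = 51.1%. Even with an 8.5-point gain in completion (31.8% to 40.3%), it looks worse once dose-1 uptake rises by more than 40.3/0.511 − 62.2 ≈ 16.6 points.

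**If the samples are pooled** (assumed rates). Let attrition be 40% in first-time invitees and 70% in previous non-attenders, the same in both arms, with 250 girls per cell.
- Control, dose 1 at 60% and 20%: (150·0.4 + 50·0.7)/200 = 47.5%.
- Incentive, dose 1 at 60% and 40%: (150·0.4 + 100·0.7)/250 = 52.0%. The chance of a significant worse result is 16%, with no change within either sample.
- Incentive, dose 1 at 75% and 25% (the same ratio, 1.25, in both samples): (187.5·0.4 + 62.5·0.7)/250 = 47.5%, so no bias.

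**A tempting replacement.** Take starters who do not complete, out of everyone randomised. With d = 8.5 and s = 25% this is 62.2 − 31.8 = 30.4% against 70.7 − 33.9 = 36.8%. At 500 per arm the chance of a significant worse result is 57%, against 12.5% for attrition among starters.

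**The case against.** The strongest reply is that nothing important rests on this test. No objective or hypothesis concerns attrition, and the key results listed in the abstract do not include it. Third-dose uptake is a primary outcome, analysed by sample among all randomised girls, and nothing says that a causal conclusion will be drawn from attrition. All of this stands, and it limits the point to a supplementary analysis. A reader might infer that the attrition test could hide a completion benefit; the document does not support that, because completion is tested directly.

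A second reply is that neither the denominator nor pooling is stated. That is correct. Dose-1 takers follow from the dose-order rule. Pooling is suggested because the sentence follows the combined model, names only the two arms, and lacks the by-sample wording of the uptake models. Both remain inferences, and an article may leave such detail to a fuller plan. Choosing all randomised girls as the denominator would restore a randomised comparison, but the last calculation shows that it invites the same misreading more often.

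A third reply is that the larger chances need harsh assumptions. This also stands: if 40% of added starters complete, the chance is only 5% to 11%.

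**Conclusion.** The concern holds as a limited one. On the natural reading, the test conditions on dose-1 uptake, which the trial's own first hypothesis expects the incentive to change, so its p-value does not carry the protection of randomisation. On the England rates, and with 8.5 to 20 points of added starters, the chance of a significant result against incentives is about 12% to 40% if a quarter of the added girls complete, 35% to 92% if none do, and 5% to 11% if 40% do. Completion is equal or better in every case. These ranges rest on assumed uptake and completion among added starters.

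A reader might also infer that pooling is what makes the comparison non-randomised. It is not: the arms were allocated in equal numbers within each sample, so pooling all randomised girls would be fair. Pooling adds bias only after restriction to starters, and only if incentives raise dose-1 uptake by a different ratio in the two samples and the samples differ in attrition.

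**What to change.** In the Statistical analysis section, replace the attrition test with a statement that attrition among girls who took dose 1 will be:
- reported descriptively by arm, separately for first-time invitees and previous non-attenders;
- shown beside dose-1 uptake;
- labelled as not a randomised comparison.

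State that any conclusion about completion rests on the dose-3 analysis of all randomised girls already planned. Do not substitute a test of starting without completing among all randomised girls, because that proportion also rises whenever incentives recruit starters who do not all finish.

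The cost is a sentence or two of text and the loss of a p-value for a supplementary comparison. No further data are needed.

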### Objectives and hypotheses

The primary objectives of the present study are:

(a) To assess the impact of financial incentives on the initial uptake (uptake of the first vaccination) and completion rates (uptake of the third vaccination) of an HPV vaccination programme.

(b) To assess the impact of financial incentives on the quality of the decision to be vaccinated as measured by attitudes towards and knowledge of the vaccination.

The secondary objective is:

(a) To assess whether the impact of financial incentives on the initial uptake and completion rates of an HPV vaccination programme is moderated by participants’ levels of social deprivation.

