## Methods/Design

### Trial design

This is a randomised controlled trial in which two independent samples of participants are separately randomised to the offer of financial incentives for getting vaccinated.

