### Procedure

The trial will be run by the Birmingham East and North Primary Care Trust in collaboration with Healthy Incentives (http://www.healthyincentives.org.uk/, a social enterprise arising as a result of a partnership between the Young Foundation and the Birmingham East and North Primary Care Trust). The Birmingham East and North PCT has employed the Birmingham Primary Care Shared Services Agency (BPCSSA) to do the following: select participants to be included in the trial; randomise them to each group and post the invitation letters. Once the letters have been sent, the BPCSSA will provide the Healthy Incentives team with the details of all the participants who have been invited, including their names, addresses, scheduled vaccination dates, the participant group (previous non-attender or previously not invited) and randomisation group (incentive or not). The vaccinations for all individuals will take place at three community clinics. The BPCSSA will schedule a number of ‘incentivised only’ sessions at these clinics to avoid any tensions caused by not incentivising all groups. Vaccinations will be carried out by nurses working with Heart of Birmingham (HOB). When attending their first vaccination session and while waiting to get vaccinated, participants will be asked to sign a consent form and complete a measure assessing the quality of their decision to get vaccinated. They will also be requested to select a date for their next vaccination. Receipt of each vaccination will be contingent on completion of all the previous doses (i.e. in order to receive the 3rd vaccination participants will need to have first completed the 1st and 2nd vaccinations), with no skipping of doses being allowed. After receiving their vaccinations, participants in the incentivised groups will be provided with the appropriate shopping vouchers. Two days prior to their 2^nd^ and 3^rd^ vaccination sessions, the Healthy Incentives team will send participants text messages reminding them of their appointments.

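### The knowledge and attitude tests appear to compare arms without the randomised sample, so they mix a shift in which sample attenders came from with any difference within a sample

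*Protocol article*

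**What the plan says.** Under Trial design, the protocol article states that "two independent samples of participants are separately randomised to the offer of financial incentives for getting vaccinated". Table 1 gives 250 girls per arm in each sample, and Sample size determination sums this as "giving 500 in each intervention arm".

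The Statistical analysis section carries this structure into uptake: "logistic regressions will be performed separately for each of the two samples". It then plans a combined uptake model, meant to test whether the effect differs between the samples, in which previous invitation "will be added as a predictor to the model, along with the intervention".

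For decision quality the same section says "differences in knowledge of the HPV vaccination between intervention and control group will be tested using the" chi-squared test, and "differences in attitudes towards the HPV vaccination will be examined via a one-way analysis of variance". Neither clause mentions the sample.

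The Procedure section places the questionnaire at the first vaccination session, where "participants will be asked to sign a consent form and complete a measure assessing the quality of their decision to get vaccinated". Girls who do not attend contribute no data. Decision quality is one of the two primary objectives under Objectives and hypotheses ("To assess the impact of financial incentives on the quality of the decision to be vaccinated as measured by attitudes towards and knowledge of the" HPV vaccine), although the Abstract calls it the secondary outcome. Hypothesis III predicts that incentives lower it.

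**The concern.** If every invited girl answered the questionnaire, the 250:250 allocation in each sample would keep the arms balanced on sample, and leaving sample out would cost little. Only attenders answer, however, and attendance is what the incentive is meant to change. Among attenders, the balance set at randomisation survives only if the incentive multiplies first-dose uptake by the same ratio in both samples. The protocol does not assume this, since it plans to examine whether the effect differs between them. Even an equal percentage-point rise changes the mix when the starting rates differ.

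Previous non-attenders are defined by not having acted on an earlier invitation, so they may plausibly hold different attitudes or knowledge. The arm-only contrast then combines two things: a change in the share of attenders from each sample, and any difference between arms within a sample. A reader of a significant result could not tell which had occurred, and a mix shift could also hide a within-sample difference of the opposite sign. Sample membership is known before randomisation, so this part can be separated.

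**Working it through.** **The plan's own figure.** The protocol gives no calculation for decision quality. Its one sample-size figure, for completion, reproduces: 32.4% against 40.9%, two-sided 5%, 80% power, pooled variance, no continuity correction gives 504 per arm, or 1008. This point does not alter it.

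**Inputs from the documents.** 250 girls per arm per sample (Table 1). First-dose uptake of 62.2% in the national catch-up campaign (Background), used here as the control rate for first-time invitees. A rise of 8.5 points (Sample size determination), stated there for completion and applied here to the first dose. Tests at 5%.

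**Assumed inputs.** All other uptake rates; the gap *d* by which previous non-attenders have a lower mean attitude, in within-sample SD units; no arm difference within either sample; no other selection. The documents give no uptake, attitude or knowledge by sample.

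**Formulas.** With first-dose uptake p_F (first-time) and p_P (previous non-attenders) in an arm:

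- Attenders: n = 250 × (p_F + p_P)
- Share from previous non-attenders: w = p_P / (p_F + p_P)
- Expected arm difference in attitude: D = −(w_inc − w_ctl) × d
- Variance in an arm: 1 + d² × w × (1 − w), averaged over the arms to give V
- SE = √[V × (1/n_ctl + 1/n_inc)]
- Rejection probability: two-sided normal test at 1.96 with shift D/SE

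**Worked case: response concentrated in previous non-attenders** (62.2% to 65% in first-time invitees, 10% to 25% in previous non-attenders).

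- n_ctl = 250 × 0.722 = 180.5; n_inc = 250 × 0.90 = 225
- w_ctl = 0.10/0.722 = 0.139; w_inc = 0.25/0.90 = 0.278
- d = 0.5: D = −0.070, SE = 0.102, rejection 10.5%
- d = 1: D = −0.139, SE = 0.108, rejection 25.3%

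**Attitude test by scenario**

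| Assumed first-dose uptake, control to incentive | Previous non-attender share, control vs incentive | Rejection, d = 0.5 | Rejection, d = 1 |
|---|---|---|---|
| Both samples 62.2% to 70.7% | 50% vs 50% | 5% | 5% |
| 62.2% to 70.7%; 20% to 28.5% | 24.3% vs 28.7% | 5.6% | 7.1% |
| 62.2% to 70.7%; 10% to 18.5% | 13.9% vs 20.7% | 6.3% | 9.9% |
| 62.2% to 65%; 10% to 25% | 13.9% vs 27.8% | 10.5% | 25.3% |

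In each row, first-time invitees are given first. If the response were confined entirely to previous non-attenders (62.2% in both arms; 10% to 30%), the rates would be about 15% and 41%. That is an extreme assumption.

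**Knowledge test.** This behaves alike. Assume 70% correct in first-time invitees and 20 points fewer in previous non-attenders. The second row then gives an arm difference of −0.9 points and rejection of 5.4%.

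**Effect of adding sample.** A simulation of the worked case at d = 1 rejected in about 25% of trials with arm alone and about 5% with arm plus sample.

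**The case against.** Four points can be made for the plan.

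*The total effect is a legitimate target.* The Discussion names a change in who attends as one way incentives might undermine informed choice, and concedes that the design cannot separate it from a change in attitudes or knowledge. Hypothesis III concerns the quality of decisions to be vaccinated, not change in any individual girl. A reader might infer from the rejection rates above that the pooled result would be spurious and would falsely support Hypothesis III. The documents do not support that: for a total effect among attenders, a mix shift caused by randomised allocation is part of what is measured. What remains is that the Discussion's caveat covers selection in general. It gives no reason to leave unseparated a component that is already recorded.

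*Pooling is not stated.* The text says that datasets are combined only for one uptake model, and either test could be run within each sample. This stands as a caution. Even so, the by-sample wording attaches only to the logistic regressions, and the knowledge clause names only intervention and control.

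*An article leaves such detail elsewhere.* This would answer a silent text. Here the tests are named, and the point concerns the tests as named.

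*The size may be negligible.* Under an equal 8.5-point rise and a 0.5 SD gap, rejection is about 6% against 5%. Since all respondents have come to be vaccinated, attitudes may differ little between samples. This stands: nothing in the documents shows a large gap.

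**Conclusion.** The point holds as a limit on what the planned tests can show, and as an improvement that is free to make. On its natural reading, the Statistical analysis section compares knowledge and attitudes by arm alone, although the samples are separately randomised and uptake is analysed by sample. That contrast is valid as a total effect among attenders, but it cannot be read as a change within a sample.

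The size is unknown. With no within-sample effect, the assumed scenarios give rejection of 5% with no mix shift, about 6% with an equal 8.5-point rise and a 0.5 SD gap, and 10% to 25% when response is concentrated in previous non-attenders and the gap is 0.5 to 1 SD. These rates describe error only if the result is read as a within-sample effect. They rest on assumed uptake by sample and assumed gaps, and on reading the two tests as pooled. Nor should a reader infer that adding sample would isolate the effect of incentives on attitudes or knowledge, since selection within each sample would remain.

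**What to change.** In the Statistical analysis section:

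- Analyse attitudes with a two-factor model, arm plus sample.
- Analyse knowledge with a Cochran-Mantel-Haenszel test stratified by sample, or a logistic model with arm and sample.
- Report the arm difference within each sample, as is already planned for uptake.
- Keep the unadjusted contrast among attenders as a descriptive total effect, labelled as such.
- Retain the Discussion's acknowledgement of selection, and say that it still applies within each sample.

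The cost is a few sentences of analysis wording and one degree of freedom. No new data are needed: the Procedure section already has participant group recorded for every invited girl, and the uptake models already require it.
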